### Treatment

#### HUGS

Participants allocated to the HUGS treatment will receive the previously evaluated 9-week manualised PND group programme followed by four sessions of mother-infant HUGS group treatment as described by [name] and colleagues[71, 72]. The 9-week PND programme consists of nine cognitive behavioural therapy sessions and three evening couple sessions (12 sessions in total). The PND programme addresses maternal mood, behavioural activation, cognitive strategies, self-esteem, adaptation of relaxation training to focus on ways to “relax on the run”, the couple relationship, getting support, practical issues, problem-solving and self-care from a cognitive behavioural therapy framework. The HUGS sessions include psychoeducation and direct intervention in the mother-infant interaction. This builds on skills developed in the PND treatment programme, allowing a short duration “booster” to change the negative trajectory of mother-infant interactions. It has been successfully trialled in a feasibility study[10]. HUGS sessions include:

Session 1 Play and physical contact: play provides interactional opportunities. It allows assessment of interactional deficits and modelling of alternative responses.

Session 2 Observing and understanding baby’s signals: essential elements of a ‘good enough’ interaction are taught to parents using guided exercises to maximise small successes.

Session 3 Parental responses to infant cues: building on cognitive strategies learnt, distorted cognitions are challenged including separating past experiences from the reality of the infant. Infants can re-awaken powerful memories of earlier family relationships[73].

Session 4 Consolidating gains: reinforcing positive interactional behaviours and cognitions about the infant (booster session).

#### Control group

Participants allocated to the control group will receive the PND programme (described above). This is followed by four non-directive group meetings of mothers, infants and a facilitator in the same surroundings as HUGS but with no direct therapeutic work (acting as an attention placebo). This controls for possible effects of group membership, social networking and therapist contact. The “Playtime” playgroup has been developed to be consistent with what is currently provided in community playgroups and which mothers generally find supportive and includes four sessions providing an opportunity for informal discussion between mothers, some psychoeducation (for example, healthy eating) as well as time to play with babies.

## Data analysis

### Power calculations

The primary outcomes are post-treatment/follow-up scores on mother-infant relationship measures: the PSI and PCERA. Based on published parameter estimates on the PSI (baseline = 282.46, σ = 41.25) from [name] and colleagues[10], a between-group difference of (δ) 33 points would take scores into the normative range on the PSI (that is, ≤250). To detect a change of 33 points, the sample size per condition is *n* = 15.7 (14.25/33)^2^ = 24.53. For the PCERA we wish to detect a medium to large effect size (2/3 SD). This is within the range of effect sizes reported for a longer mother-infant intervention measured with the PCERA[45, 46]. This yields *n* = 15.7 (1/.66)^2^ = 36.04, which rounds to 40. Taking the highest estimate (PCERA) and allowing 10% attrition, the adjusted group is *n** = *n*/(1-.10)^2^ = 49.38, which rounds to 50 depressed women in each condition.

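### The sample-size derivation is wrong as printed, on the conservative side: 36.04 is carried as 40 and 10% attrition is applied squared, so a requirement of about 41-42 per arm becomes 50

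*Protocol article*

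**What the plan says.** All the steps are in the protocol article, Data analysis, Power calculations.

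- **PSI.** The inputs are "Based on published parameter estimates on the PSI (baseline = 282.46, σ = 41.25") and a between-group difference of 33 points. The equation is printed as "15.7 (14.25/33)^2^ = 24.53".
- **PCERA.** The target is given in words, "For the PCERA we wish to detect a medium to large effect size (2/3 SD"), and entered as 0.66: "15.7 (1/.66)^2^ = 36.04, which rounds to 40".
- **Attrition.** The larger of the two estimates is taken forward: "Taking the highest estimate (PCERA) and allowing 10% attrition, the adjusted group is" n/(1-.10)^2, with the result "49.38, which rounds to 50 depressed women in each condition".

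The Design section adopts 50 per condition, 100 in total. The article states neither a significance level nor a power.

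**The concern.** The section is the only justification shown for 100 participants, and its steps do not lead from its inputs to its result. One equation is false as printed. One step called rounding adds almost four women per arm. One inflation factor does not match the purpose given for it.

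What is at stake is the account of the design rather than its adequacy. The printed text attributes the whole of 50 per arm to a 0.66 SD effect with 10% loss. A reader who accepts that will think there is no slack beyond 10% loss. The slack is in fact considerable, but the article neither names it nor explains it, so it cannot be set knowingly against higher loss or any other demand on the sample.

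**Working it through.** **Inputs** (all from Power calculations): multiplier 15.7; PSI σ 41.25, printed as 14.25 in the equation; PSI difference 33; PCERA effect 0.66 SD; attrition 10%.

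**What 15.7 implies.** For two means, n per arm = 2(z_alpha + z_power)^2 (SD/difference)^2. With two-sided 5% and 80% power, 2(1.960 + 0.842)^2 = 15.70. At 90% power the multiplier would be 21.01, and with one-sided 5% at 80% power it would be 12.37. Only the first matches, so two-sided 5% and 80% power are inferred here, not quoted.

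**The plan's own figures**

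| Step | Calculation | Result | Printed |
|---|---|---|---|
| PSI, as printed | 15.7 × (14.25/33)^2 | 2.93 | 24.53 |
| PSI, with stated σ | 15.7 × (41.25/33)^2 | 24.53 | 24.53 |
| PCERA | 15.7/0.66^2 | 36.04 | 36.04 |
| Rounding | 36.04 rounded up | 37 | 40 |
| Attrition, squared | 40/0.81 | 49.38 | 49.38 |

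The PSI digits are transposed in the equation only. The PSI result is below the PCERA's and is not carried forward, so this slip contributes nothing to the 50.

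**Attrition.** If a fraction R is lost, n(1-R) complete, so the inflated size is n/(1-R). The square arises in a different problem: if a fraction R do not adhere but are still measured, the average effect shrinks to (1-R) of its size, and n grows by 1/(1-R)^2.

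**Corrected chain**

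- Both steps corrected: 36.04/0.90 = 40.04, so 41 per arm; or 37/0.90 = 41.1, so 42 per arm. That is 82-84 in total.
- Only the attrition factor corrected: 40/0.90 = 44.4, so 45 per arm.
- Only the rounding corrected: 36.04/0.81 = 44.5, so 45 per arm; from 37, 37/0.81 = 45.7, so 46.

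The printed 49.38 needs both departures together. Using 2/3 in place of 0.66 does not help: 15.7/(2/3)^2 = 35.3, which is smaller.

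**What 50 per arm provides**

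- With 10% loss, 50 × 0.90 = 45 complete per arm. Power for 0.66 SD is 87% by the t-test (88% by the normal approximation).
- With 45 per arm, the effect detectable at 80% power is sqrt(15.7/45) = 0.59 SD by the normal approximation, and about 0.60 SD by the t-test.
- Loss that still leaves 37 per arm: 1 - 37/50 = 26%.

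**If the square was meant for non-adherence**, loss to follow-up has to be added: 37/(0.81 × 0.90) = 50.75 per arm, or 49.4 from the unrounded 36.04.

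**The case against.** The strongest defence is that little here matters. The SD is a typing slip with a correct result. Every step is printed, so nothing is concealed. The two steps that set the sample size both err upward, and no decision or analysis changes. All of that stands, and it limits the point to a correction of the text.

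It can also be argued that attrition may mean dropping out of sessions while still being assessed, in which case the square is a recognised adjustment. The Analyses section plans intention-to-treat with imputation so that all 100 are analysed, and mentions session attendance. The reading is possible, but Power calculations does not give it, and Analyses takes up non-compliance only as an exploratory dose-response question. Even granting the square, the result is 45 or 46 per arm, not 50.

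A reader might go further and infer one of the following. The document supports none of them.

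- *The trial is underpowered.* On the stated attrition reading it is larger than needed. A shortfall on the non-adherence reading appears only if one starts from the unexplained 40. From the actual requirement, 50 is within one woman per arm.
- *The wrong SD undermines the sample size.* The PSI line does not drive it.
- *The article claims 80% power.* It states no power; the figure is implied by 15.7.
- *The 40 already contains the attrition*, since 36.04/0.90 = 40.04. This is conjecture; the article calls the step rounding.

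**Conclusion.** The derivation is wrong as printed, in a conservative direction. The stated inputs require about 41-42 per arm; the plan arrives at 50, an excess of 8-9 per arm (16-18 in total). That excess comes from carrying 40 in place of 37 and from squaring the 10% factor. The transposed SD is a separate slip with no effect on enrolment.

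The size of the excess rests on three assumptions: two-sided 5% and 80% power, as implied by the multiplier; a simple comparison of two means, as in the plan's own formula; and attrition in its usual sense of women lost to follow-up. If the 10% was meant as non-adherence, the excess disappears once attrition is added, and 50 per arm is about at the requirement with no margin. The adequacy of 50 per arm is not in doubt on the stated reading; its justification is.

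**What to change.** Keep 50 per arm and restate the justification:

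1. Print 41.25 in the PSI equation.
2. State the significance level, its sidedness and the power behind 15.7.
3. Carry 37 for the PCERA.
4. Apply attrition as n/(1-0.10), giving 37/0.90 = 41.1, so 42 per arm.
5. State that 50 per arm exceeds this, and what the excess provides: about 87% power for 0.66 SD, or 80% power for about 0.60 SD, with 45 completers per arm; or tolerance of up to about 26% loss.
6. If the squared factor was intended for non-adherence, say so, add attrition as a separate term, and acknowledge that 50 per arm then leaves no margin.

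The cost is a correction of one paragraph. Enrolment, conduct and analysis do not change.

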### Analyses

Data will be screened to: (i) check for data entry errors; and (ii) test the assumptions underlying parametric procedures. For each outcome, *a priori* treatment comparisons will be conducted by fitting models controlling for baseline values, to yield direct comparisons of the effectiveness of the two conditions. Intention-to-treat principles following CONSORT guidelines will prevent systematic bias[59]. Baseline data will be secured prior to allocation, and missing values will be scrutinized to check for non-random distribution and imputed at the case level using gold-standard maximum likelihood methods (Multiple Imputation). Primary analyses will be executed twice: once using observed data, and once using multiple imputation methods given by Schafer[74], so that all 100 participants will be analysed in their allocated treatment condition. To assess how non-compliance affects results, the dose-response relationship between session attendance and level of clinical improvement will be explored. Primary data analyses will be conducted fully blind to treatment allocation (via coded treatment labels).

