### Design

The proposed research is a multi-site, parallel, two-group RCT involving 100 participants (n = 50 in each condition) and will be conducted in line with CONSORT standards ([58, 59]; http://www.consort-statement.org/). Figure 1 shows the design of the study.

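### HUGS and Playtime are delivered in arm-specific groups, but the sample size has no design effect and the described analysis names no treatment-group term

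*Protocol article*

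**What the plan says.** The Design section plans "100 participants (n = 50 in each condition". The Randomisation section allocates individual women before the postnatal depression (PND) programme starts, stratified by site.

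Treatment is in groups throughout. The HUGS arm receives a "9-week manualised PND group programme followed by four sessions of mother-infant HUGS group treatment". The control arm receives the same PND programme and then "four non-directive group meetings of mothers, infants and a facilitator". The Control group section says of this arrangement: "This controls for possible effects of group membership, social networking and therapist contact".

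The Power calculations section uses n = 15.7(σ/δ)² per arm for both primary outcomes, the Parenting Stress Index (PSI) and the Parent-child Early Relational Assessment (PCERA). It then continues: "Taking the highest estimate (PCERA) and allowing 10% attrition, the adjusted group is" 49.38, rounded to 50. It gives no design effect, ICC or group size.

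The Analyses section says that "treatment comparisons will be conducted by fitting models controlling for baseline values, to yield direct comparisons of the effectiveness of the two conditions". Baseline adjustment is the only feature of the model that it names.

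**The concern.** A HUGS group contains only HUGS women and a Playtime group only Playtime women. If women in the same group end up more alike than women in different groups, the group-to-group variation goes straight into the variance of the treatment difference. A model with baseline adjustment alone leaves that part out. Its confidence interval is then too narrow and its p-value too small.

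The playgroup control does not solve this. Giving both arms group contact balances the average effect of being in a group. It does not remove the correlation among women who shared one.

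The sample size has the same gap: correlated outcomes carry less information than the same number of independent ones. With perhaps 15 treatment groups in all (90 women at 6 per group), a few unusual groups could weigh heavily on the estimated effect.

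**Working it through.** **1. Reproduce the plan's figures.**
- Multiplier: 2(1.960 + 0.842)² = 15.70, which is two-sided 5% and 80% power. Other common choices do not match: two-sided 5% with 90% power gives 21.01, and one-sided 5% with 80% gives 12.37.
- PCERA: 15.7 × (1/0.66)² = 36.04, which the plan rounds to 40. Then 40/(0.90)² = 49.38, rounded to 50.
- PSI: 15.7 × (41.25/33)² = 24.53. PCERA therefore drives the size.

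The calculation reproduces and is the independent-observations formula.

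**2. Slack under independence.** Power = Φ(0.66 × √(n/2) − 1.96).
- n = 36: 80.0%
- n = 40: 83.9%
- n = 45 (50 less 10%): 87.9%

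The slack comes from rounding 36.04 up to 40 and from squaring the attrition factor.

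**3. Assumptions, none of them in the document.** Group size m = 4 to 10, ICC = 0.02 to 0.10, central case m = 6 and ICC = 0.05. Design effect DE = 1 + (m − 1) × ICC, so the central case is 1 + 5 × 0.05 = 1.25 and the range is 1.06 to 1.90.

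**4. True error of a nominal 5% test with no group term.** 2(1 − Φ(1.96/√DE)). At DE = 1.25, 1.96/1.118 = 1.753, which gives 8.0%.

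**5. Power for 0.66 SD with a valid test.** Normal approximation: replace n by n/DE. At 45 per arm and DE = 1.25, n/DE = 36 and power is 80%. Group-level version: noncentral t with 2n/m − 2 degrees of freedom, which is 90/6 − 2 = 13 in the central case.

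| m | ICC | DE | True error | Power, 45 per arm, normal | Power, 40 per arm, normal | Power, 45 per arm, group-level df |
|---|---|---|---|---|---|---|
| 4 | 0.02 | 1.06 | 5.7% | 86% | 82% | 82.5% |
| 6 | 0.02 | 1.10 | 6.2% | 85% | 80% | 79% |
| 6 | 0.05 | 1.25 | 8.0% | 80% | 75% | 73.5% |
| 8 | 0.05 | 1.35 | 9.2% | 77% | 72% | 67% |
| 6 | 0.10 | 1.50 | 11.0% | 72% | 67% | 66% |
| 10 | 0.10 | 1.90 | 15.5% | 62% | 57% | 50% |

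The PSI has more room: at 40 per arm, ICC 0.05 and m = 6 to 8, power is 87% to 89% by normal approximation.

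**6. Effect of baseline adjustment.** The plan sizes on the raw SD but adjusts for baseline. Assume a baseline–outcome correlation r of 0.3 to 0.5 (not in the document) and divide the SD by adjusting it to SD × √(1 − r²), so that 0.66 becomes 0.69 to 0.76. In the central case with 45 per arm, power is then 84% to 90% by normal approximation and 77% to 85% on 13 degrees of freedom. This does not change step 4.

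**7. Enrolment at DE = 1.25.** 36.04 × 1.25 = 45.05 analysed per arm. Dividing by 0.90 gives 50.1 enrolled per arm. The plan's own divisor, 0.81, gives 55.6.

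**The case against.** The strongest reply is that the analysis half rests on silence. The Analyses section does not say that women are treated as independent, and it names no class of model. A random group intercept would fit its wording, and a full protocol or analysis plan that is not shown could supply one. That stands, so the error-rate figures are conditional on fitting the model as the article describes it. The reply does not reach the sample size, which is worked out in full in the article and makes no allowance for clustering.

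Three stronger readings are tempting but unsupported.
- A reader might infer that 80% power and 5% error are stated targets that the design misses. Neither figure appears in the article; both are implied by 15.7.
- A reader might infer that the trial is underpowered. The slack in the planned size keeps power at about 80% in the central case by normal approximation, and baseline adjustment may raise it. A shortfall depends on group size, ICC, attrition and degrees of freedom.
- A reader might count the PND groups as a further source of inflation. The article does not say whether those groups mix the two arms. Women are randomised before the programme, so they may, and that layer would then be crossed with arm and need not inflate the error.

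It is also fair that stratifying by site should largely balance between-site differences across arms. If part of the within-group correlation is really site-level, the figures above overstate the effect.

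**Conclusion.** The point holds for the HUGS and Playtime groups. The sample size ignores clustering by treatment group, and the analysis as described names nothing that would account for it.

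If no group term is fitted, the true error of a nominal 5% test is above 5% for any positive ICC: 8.0% at 6 women per group and ICC 0.05, and 5.7% to 15.5% over the assumed range. These sizes rest wholly on assumed group sizes and ICCs.

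The loss of power is a possibility, not a finding. For PCERA in the central case with 45 analysed per arm it is about 80% by normal approximation and about 74% on group-level degrees of freedom, before any gain from baseline adjustment. A claim that 80% power holds up to a design effect of 1.25 would therefore be unsafe, because it relies on the normal approximation.

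**What to change.** **Analysis.** Record which HUGS or Playtime group each woman attended. Analyse each primary outcome with the baseline-adjusted model plus a random intercept for that group, using small-sample degrees of freedom such as Kenward-Roger. Specify this before the analysis, so that it is not a post hoc choice.

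**Sample size.** Keep 50 per arm. State that 15.7 corresponds to two-sided 5% and 80% power. Give an explicit group size and ICC range, and report power as a range on the same degrees of freedom as the analysis. Use one stated attrition divisor: at a design effect of 1.25, dividing by 0.90 gives 50.1 per arm and dividing by 0.81 gives 55.6. Do not claim that 80% power holds up to a design effect of 1.25.

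**Cost.** No extra participants; one more recorded variable, which attendance records should already supply, and revised wording. The downside is wider intervals and a less favourable power statement.

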## Discussion

PND is prevalent and there is accumulating evidence that PND results in early dysfunctional relationships between mothers and infants with long-term consequences on infant brain development, cognitive functioning, emotional health and behaviour. For these reasons, there is a critical need for interventions addressing mother-infant difficulties following PND to explore whether later difficulties can be prevented. Mother-infant difficulties need to be addressed as soon as possible to prevent cumulative detrimental effects on child development[9, 10]. The HUGS intervention is innovative both in its brevity and conceptualisation. The vast majority of existing mother-infant interventions are intensive and/or long term. A brief, four-session intervention would be cost effective and could be rolled out to large numbers. Given the high prevalence of PND and that 70% of women with PND have relationship difficulties with their infants[9], a highly novel contribution of this study is the development of a brief, effective intervention that is easily taken up by primary care providers and added to existing treatment for PND.

Given the world-wide advocacy for universal screening for depression perinatally[75], there will be a sharp increase in the number of women identified and managed for their depressive condition. Best-practice pathways for women identified as being depressed perinatally need to be developed. A brief mother-infant intervention that can be added onto an existing treatment for PND would be an innovative way to provide a care pathway. In light of this, we developed the HUGS programme, a cost-effective, early intervention to bolster and protect the mother-infant relationship and prevent the intergenerational transmission of risk. The significance of early childhood experiences on adult health later in life is evident and, as such, the social and economic benefits of such an intervention are substantial.

## Trial status

At the time of manuscript submission, participant recruitment had not been completed. The trial is ongoing.

## Authors’ original submitted files for images

Below are the links to the authors’ original submitted files for images. Authors’ original file for figure 1

## Abbreviations

HUGS: Happiness Understanding Giving and Sharing
PCERA: Parent-child Early Relational Assessment
PND: postnatal depression
PSI: Parenting Stress Index
RCT: randomised controlled trial.
